# Multidomain interventions for non-pharmacological enhancement (MINE) program in Chinese older adults with mild cognitive impairment: a multicenter randomized controlled trial protocol

**DOI:** 10.1186/s12883-023-03390-5

**Published:** 2023-09-28

**Keywords:** Mild cognitive impairment, Randomized Controlled Trial, Multidomain Interventions, Non-pharmacological, Older adults

## Abstract

**Background:**

Dementia is characterized by progressive neurodegeneration and therefore early intervention could have the best chance of preserving brain health. There are significant differences in health awareness, living customs, and daily behaviors among Chinese older adults compared to Europeans and Americans. Because the synergistic benefits of multidomain non-pharmacological interventions are consistent with the multifactorial pathogenicity of MCI, such interventions are more appealing, easier to adhere to, and more relevant to daily life than single-mode interventions. One of the aims of this study is to verify the effect of multidomain intervention strategies for MCI patients based on Chinese population characteristics, and the other is to establish a biobank and image database to investigate the pathogenesis and pathways of cognitive impairment.

**Methods:**

Our study was designed as a national multicenter, community-based randomized controlled trial (RCT). Twelve medical institutions in ten Chinese cities will participate in our study from 2020 to 2024, and 1080 community residents aged 50 and above will be enrolled as participants. Each sub-center will be responsible for 90 participants (30 people per community) across three communities (non-contact control group, health education group, and multidomain intervention group). The community will be the basic unit of the present study, and all participants in each community will receive the same intervention/control measure. Three working groups are set up in each sub-center to manage the three communities independently to minimize interference at the implementation level between the groups. The multidomain intervention group will receive integrated interventions including exercise, nutrition, sleep, health education and mindfulness meditation. All data generated by the research will be analyzed and processed by statistical software (such as SPSS 21.0, Python 3.0, etc.), and part of the research data will be displayed in the form of graphs and tables.

**Discussion:**

In order to achieve a high-quality community intervention study, it is crucial to have a well-designed experimental protocol that follows rigorous scientific methodology. In addition, effective management of quality control measures and monitoring compliance throughout the study process are essential components. This study provides a detailed discussion of stakeholder compliance, research quality control, potential harm and mitigation, auditing, and future plans in order to better address research issues.

**Trial registration:**

: ChiCTR2000035012 (July 27, 2020).

**Supplementary Information:**

The online version contains supplementary material available at 10.1186/s12883-023-03390-5.

## Background

Dementia is a clinical syndrome characterized by chronic, acquired, and progressive mental decline and memory loss, resulting in an inability to perform daily activities. Alzheimer’s disease (AD) is the most common, accounting for 60–80% of all dementia cases [1].

World Health Organization (WHO) statistics indicate that a new AD patient is diagnosed every three seconds globally. According to the World Alzheimer’s Disease Report 2019, approximately 50 million people are suffering from AD around the globe. This number is expected to rise to 152 million by 2050, with an annual global economic burden of approximately one trillion US dollars [2].

China has the highest number of dementia patients in the world. According to the “Healthy China Action (2019–2030)” released in 2019, the prevalence rate of AD among people aged 65 and above is 5.56%, accounting for 20% of global patients, up to 10 million, ranking first in the world. By 2050, it is expected to exceed 40 million [3].

The course of AD is obscure, and it is not easy to diagnose at an early stage. Concurrently, the exact etiology and pathogenesis of the disease are still unknown, and treatment methods are still being explored. Therefore, early prevention, diagnosis, and intervention have emerged as the primary focus of global research [4]. The recent Lancet Commission on Neurology states that action to prevent dementia must be taken immediately. The latest research knowledge and effective prevention programs must be implemented without delay. Meanwhile, the Action Plan for Healthy China (2019–2030) has clearly stated the goal of controlling the future growth rate of dementia prevalence [5].

Mild cognitive impairment (MCI) is an intermediate stage between normal aging and dementia. The latest evidence reveals that the prevalence of MCI among older adults aged 60–64 years has increased from 6.7 to 25.2% among older adults aged 80–84 [6]. However, the average prevalence of MCI in China is approximately 20.8% [7]. After three years, up to 44% of MCI patients can be converted into AD, which is ten times higher than the general population, and the probability of developing AD within five years is as high as 70%, which is the main factor for the occurrence of AD [3]. Therefore, there is a “time window” for intervention to delay disease progression and treatment. Existing evidence indicates that intervention at this stage can effectively slow or prevent MCI from progressing to dementia [8], which significantly impacts promoting healthy aging in China.

At present, some research evidence suggests that single intervention such as exercise, nutrition, sleep and meditation had a positive effect on promoting cognitive function.

### Exercise and MCI

The latest American Academy of Neurology (AAN) guidelines [9] believe that regular exercise in MCI patients can help improve cognitive function, which is recommended as part of the overall treatment. The guideline recommendation is (level B) that exercise twice a week for six months may help improve memory in people with mild cognitive impairment [9]. A network meta-analysis of 71 studies compared the effects of various types of exercise (aerobic exercise, resistance exercise, compound exercise, mind-body exercise, whole-body vibration, and finger exercises) on overall cognitive function and specific dimensions of cognitive function in patients with MCI and dementia. The optimal types of exercise interventions for MCI and dementia patients with different dimensions of cognitive function were revealed, providing evidence support for the formulation of exercise prescription and the implementation of individualized exercise intervention [10].

### Nutrition and MCI

Pathology, heredity, environment, and living habits affect cognitive function in aging, and dietary intake in living habits is one of the hot research areas in recent years. Numerous epidemiological studies reveal that diet is related to cognitive function and that healthy eating habits protect cognitive function [11]. Currently, studies on the diet of older adults with cognitive dysfunction are being conducted. Substantial evidence supports that changing diet and nutrition can help maintain good cognitive health, mood, immune function, and vascular status. The earlier the change, the better the effect. The Mediterranean-Dash diet Intervention for Neurodegenerative Delay (MIND) studies demonstrated that the MIND diet pattern could reduce the risk of AD and are more effective than the Mediterranean diet alone in slowing cognitive decline and promoting brain health [12, 13]. A follow-up study in 2015 revealed that the brain age of older adults who adopted the MIND diet was 7.5 years younger on average than the control group [14].

### Sleep and MCI

Studies demonstrated that patients with MCI have impaired sleep-dependent memory consolidation, as the dentate gyrus volume shrinks in the MCI group compared with the control group. In addition, the duration of sleep spindles is shorter, implying that the duration of sleep spindles may be related to memory consolidation. A cross-sectional study of 4,417 older adults indicated that higher beta-amyloid deposition was associated with shorter sleep duration, and both shorter (< 6 h) and longer (> 9 h) sleep duration was associated with cognitive decline and severe depression [15]. The previous study of this research team revealed that 43.8% of older adults with MCI in the community had sleep disorders.

### Meditation and MCI

Mindfulness meditation can help patients with MCI as a non-pharmacological treatment that is safe and effective. A study revealed that participants who completed a mindfulness-based meditation stress reduction program improved on measures of cognitive function and well-being, as well as positive changes in the hippocampus and other brain regions associated with cognitive decline. Most people who practice mindfulness meditation can master the fundamental principles of mindfulness, implying that memory impairment with MCI does not preclude learning this skill and that adults with MCI can improve their cognitive reserve by learning mindfulness meditation [16].

Multidimensional interventions are those that have two or more dimensions. Because the synergistic benefits generated by multidomain interventions are consistent with the multifactorial nature of MCI, international studies demonstrated that multidomain interventions have more significant benefits in improving cognitive impairment than cognitive training or exercise alone, such as several large multidomain RCTs of lifestyle in Europe Finnish Geriatric Intervention Study to Prevent Cognitive Impairment and Disability (FINGER; NCT01041989) trial in Finland, The French Multidomain Alzheimer Preventive Trial (MAPT; NCT00672685) and the Dutch Prevention of Dementia by Intensive Vascular Care (Pre-DIVA; ISRCTN29711771) trial, both of which revealed that after intervention in multiple fields such as diet, exercise, sleep, cognitive training, and vascular risk monitoring, there was a significant improvement in cognition [17, 18]. For example, the FINGER experiment in Finland indicated that the executive function and processing speed of the intervention group increased by 83% and 150%, respectively. In addition, there were significant intervention effects on other secondary outcomes such as body mass index (BMI), eating habits, and physical activity. The improvement of primary and secondary cognitive outcomes increased by 25–150% compared to the control group.

Compared with single intervention, the multi-domain intervention subjects have higher compliance, easier to adhere to, and more interactivity. However, compared with Europeans and North Americans, there are differences in protein intake, frequency of exercise, cooking/eating patterns, personal hobbies and other behaviors and lifestyles among older Asians [19–22]. There is currently insufficient evidence of early multidomain intervention studies for the older adult MCI population in Asia, particularly in Southeast Asia.

### Explanation for choice of comparators

The main aim of this study is to evaluate the effectiveness of multidomain cognitive intervention. Subjects in the non-contact control group (without any intervention) will be selected as the control group to compare the effect evaluation of different intervention intensification (multi-domain collaborative intervention and traditional health education).

### Objectives

A randomized controlled trial will be used to investigate and validate a multidimensional intervention strategy for MCI patients based on Chinese population characteristics.To build a community non-drug multidimensional intervention biobank for MCI patients and to investigate the disease mechanism and cognitive impairment pathway.

## Methods

### Trial design and study setting

The present study was designed as a multicenter, national, community-based RCT (2020–2024). We followed the Standard Protocol Items: Recommendations for Interventional Trials guidelines (SPIRIT 2013) in developing this protocol.

This program was led by the West China Hospital of Sichuan University (WCHSCU). We advertised for research partners on the National Clinical Research Center for Geriatrics (NCRCG) platform, and 27 hospitals responded. After one-on-one communication, we decided that the project would be carried out simultaneously with 12 sub-center research partners in 10 major Chinese cities. The present study will be conducted in Chengdu City (WCHSCU, Chengdu Fifth People’s Hospital, and The First Veterans hospital of Sichuan Province), Daqing City (Daqing Long Nan Hospital), Nanning City (The First People’s Hospital of Nanning), Hangzhou City (The First Affiliated Hospital, Zhejiang University School of Medicine), Lanzhou City (The First Hospital of Lanzhou University), Nanjing City (Jiangsu Province Geriatric Hospital), Yibin City (The Second People’s Hospital of Yibin), Changchun City (Jilin Provincial People’s Hospital), Qingdao City (Qingdao Municipal Hospital), Tai’an City (Taian City Central Hospital). The signing of study cooperation agreements between WCHSCU and each sub-center and ethical application in each sub-center is in progress. As of May 2023, eight of the 12 sub-centers had completed ethical applications and signed research cooperation agreements, while the remaining four partners are still in the process.

In each sub-center city, three communities are selected: the non-contact control group, the health education group, and the multidimensional intervention group. According to the eligibility criteria, 30 participants from each community were selected to participate in the study. All participants from the same community will receive the same intervention, and all participants will participate in the study for a period of six months, the difference is that participants in different communities receive different interventions.

### Participants eligibility criteria and timeline

All participants in the present study are from natural population communities, all intervention staff must pass the uniform training and examination organized by the NCRCG before carrying out the specific intervention work.

In order to find MCI subjects in the community more accurately and quickly, our team set the following subject qualification criteria in accordance with “2018 Chinese Guidelines for Diagnosis and Treatment of Dementia and Cognitive Impairment (V): Diagnosis and Treatment of Mild Cognitive Impairment“ [23]. The following screening eligibility criteria are used:

#### Inclusion criteria

The participants were community residents aged 50 and above (age is subject to ID card).The chief complaint of forgetfulness (self-reported memory deterioration in the last five years) or memory deterioration confirmed by a researcher.The baseline Montreal Cognitive Assessment (MoCA) score of less than 26/30 are used primarily to include subjects with cognitive dysfunction; Mini-mental Status Examination (MMSE) scores greater than 22 are primarily used to include subjects with non-severe dementia [24].On the daily instrumental activity scale, Lawton and Brody scored more than 6/8.Being able to live in their own homes rather than hospitals or long-term care facilities.Can read and write by themselves.Do not take anti-dementia medications (e.g., donepezil, galantamine) recently or during the study period.Sign the informed consent form, confirming that you have been informed of all relevant contents of the trial.Able to walk four meters independently with or without a walker.Physical Activity Readiness Questionnaire (PAR-Q) scale confirmed that the participants were healthy enough to participate in the relevant exercise.By utilizing the multi-nutritional assessment short form (MNA-SF) questionnaire to assess nutritional status and also understanding the subject’s history of food allergies, clinical nutrition experts evaluate if they are eligible for nutritional intervention.The Pittsburgh Sleep Quality Index (PSQI) showed no serious sleep disorder.Previous medical history investigations indicate no serious mental illness and no current psychological or psychiatric treatment.Complete all assessment contents and sign the informed consent form.

#### Exclusion criteria

In the past three months, engaged in moderate-intensity physical exercise for physical training for more than 60 min per week;Diagnosed with any type of dementia.Impaired cognitive function caused by neurodegenerative diseases (e.g., multiple sclerosis, Parkinson’s disease, Huntington’s disease, frontotemporal dementia) but not AD and vascular cognitive impairment.Have a high risk of adverse cardiovascular events during exercise, or fail to adjust their activities according to the guidance of rehabilitation exercise experts, or achieve the recommended activity level through understanding.Diagnosis of severe peripheral neuropathy or severe musculoskeletal or joint diseases that impair mobility.Using medications that may impair cognitive function, such as anticholinergics, including drugs with significant anticholinergic properties (e.g., amitriptyline), major sedatives (i.e., typical and atypical antipsychotics), and anticonvulsants (e.g., gabapentin, and valproate).Any hormone therapy (estrogen, progesterone, or testosterone) received within the previous 24 months.Plan to or have participated in concurrent clinical drug or exercise trials.The older adult with metal in the body, such as dentures (not to be removed), cardiac pacemakers, artificial hip joints, steel plates, steel nails, stents, and other metals, so that the Functional Magnetic Resonance Imaging (MRI) test results are not affected.Community residents diagnosed with depression or delirium by a medical institution will not be able to participate in this study.

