The data platform manager screened out the list of eligible participants based on the assessment results recorded in the database and submitted it to the PI for the second round of review;The principal investigator (PI) reviewed the eligibility conditions of the participants in the list again based on eligibility criteria and submitted the list to the community manager for the third round of confirmation;Community managers conducted community on-site interviews with the community participants, informed them about the content of the informed consent again, and signed the informed consent will be by the participants themselves.

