### Interventions

Our study will be mainly composed of Multidimensional intervention group, Health education intervention group and non-contact control group. The implementation scenarios of all research processes (except MRI) under this research project will be completed in the community. Each study group receives varying levels of cognitive health risk factor intervention, as presented in Table 1.

**Table 1 Tab1:** Interventions and groups setting

Section	Non-contact control group	Health Education Intervention	Multidimensional Intervention
Exercise intervention	**×**	**×**	**√**
Sleep intervention	**×**	**×**	**√**
Meditation intervention	**×**	**×**	**√**
Dietary intervention	**×**	**×**	**√**
Health education intervention	**×**	**√**	**√**

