All subjects are not allowed to participate in other lifestyle intervention or drug intervention trials during this study period. During the study period, if a subject does participate in another lifestyle intervention or drug trial, we will inform them that although they can continue to participate in the program, they will not be provided with follow-up evaluations and related tests (fMRI, blood tests, etc.) and their personal data will be disregarded and not used in the analysis.

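### The entry criterion bars only concurrent drug or exercise trials, but the conduct rule bars every lifestyle-intervention or drug trial, so a resident in a diet or sleep trial can be enrolled and then removed after allocation.

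*Protocol article*

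**What the plan says.** Two sections of the protocol article deal with participation in other trials.

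- **Exclusion criteria.** The only criterion on other trials excludes those who "Plan to or have participated in concurrent clinical drug or exercise trials". It names two kinds of trial: drug and exercise.
- **Adherence strategy.** The rule for the study period is: "All subjects are not allowed to participate in other lifestyle intervention or drug intervention trials during this study period". It also names two kinds, lifestyle intervention and drug. Those who do take part in such a trial may stay in the programme, but "they will not be provided with follow-up evaluations and related tests", and "their personal data will be disregarded and not used in the analysis".

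The article does not define lifestyle intervention. Its Background, under Meditation and MCI, describes "several large multidomain RCTs of lifestyle in Europe" and lists diet, exercise, sleep and cognitive training among the fields that those trials covered. Lifestyle is therefore used there for more than exercise.

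**The concern.** An entry criterion and a conduct rule on the same matter should have the same scope. Here the conduct rule is wider, so some residents satisfy the criteria when they are screened and conflict with the rule once the study period starts, without having changed anything.

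The consequence is out of proportion to the cause. Had the criterion been wide enough, such a resident would be a screen failure: outside the comparison, and with little spent. Under the present text the resident is enrolled into a community whose arm is already fixed and is then lost to follow-up and analysis. A loss after allocation falls inside the comparison between arms; a screen failure does not. The baseline tests and the place in the community are used up as well.

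**Working it through.** No figure in the plan depends on this point, so the check is a comparison of the text.

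**1. The two scopes.**

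| Kind of concurrent trial | Barred at entry (Exclusion criteria) | Barred during the study (Adherence strategy) |
|---|---|---|
| Drug | yes | yes |
| Exercise, alone or as a component | yes | yes |
| Diet, sleep or cognitive training, without exercise | no | yes, on the Background's use of lifestyle |
| Meditation or health education only | no | by inference only |

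The third row is the gap. The fourth is less certain: the Background list does not name meditation or health education, and their inclusion rests on their being components of this trial's own multidomain programme (Table 1).

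**2. Does another criterion close the gap?** Three inclusion criteria come near it.

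- The medical-history criterion requires "no serious mental illness and no current psychological or psychiatric treatment". It concerns treatment, not trials. At most it catches a meditation trial run as therapy.
- Nutrition experts judge suitability for the dietary component. They might notice a resident on a trial diet, but the criterion does not exclude one for that.
- The sleep-quality criterion concerns the severity of sleep disorder, not exposure to a sleep trial.

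**3. Does a later check close it?** Recruitment and screening describes three rounds of review. The data platform manager filters on recorded assessment results. The principal investigator then "reviewed the eligibility conditions of the participants in the list again based on eligibility criteria", that is, applies the same written list. The community manager interviews the resident on site and goes through consent again. None of these adds a wider exclusion for other trials.

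**4. When is the resident removed?** MRI and biological sampling come in the last of the four screening steps, before the participant list is final. Under Sequence generation, the arm of each community is fixed in the first step, and individuals are drawn in the second from candidates who have finished the assessments. A resident in the gap has therefore already used the baseline tests and, if drawn, holds one of 30 places: 1/30 = 3.3% of that community's sample. The conduct rule takes effect only after that.

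**The case against.** The strongest reply is that this is a difference of wording with little behind it. Few residents will be in a diet, sleep or cognitive-training trial without an exercise component. Such a resident could also leave the other trial before starting, and the repeated consent interview might tell them to. The consent text is not shown, so this cannot be settled. All of this limits the size of the problem, and it means that a breach from the first day is possible but not certain. The mismatch between the two rules remains.

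Three stronger readings are tempting, and the document does not support them.

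- **That the gap dilutes the contrast between arms.** A detected participant is dropped from the analysis and so cannot dilute it. An undetected one might, but a wider criterion that also relies on self-report could miss the same person. If such exposure were equally common in all arms and effects were additive, the difference between arms would not change.
- **That every domain except exercise is open to outside trials.** Any trial with an exercise component is already barred, a meditation trial given as therapy may be caught by the medical-history criterion, and health education comes under lifestyle only by inference.
- **That a look-back period is missing.** Neither rule sets one, so they do not conflict on this. A resident who has finished another trial before entry does not break the conduct rule. A washout would be a design preference.

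**Conclusion.** The point holds as an inconsistency between two stated rules. A resident in a non-exercise lifestyle trial can satisfy the written criteria and then, under the Adherence strategy, lose follow-up and be left out of the analysis after allocation, for a condition that could have been known at screening.

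The weight is minor. The article gives nothing from which to estimate how many people are affected. The number is probably small, and no effect on the treatment estimate is demonstrated. The conclusion assumes that diet, sleep and cognitive training count as lifestyle, as the Background suggests, and that the resident stays in the other trial once this one starts. One such field is enough for the mismatch to exist.

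**What to change.** Reconcile the Exclusion criteria with the Adherence strategy so that both cover the same trials. The entry criterion would exclude current or planned participation, during the study period, in any other drug or lifestyle-intervention trial. State once what lifestyle intervention includes, and use that meaning in both places. Ask the question at the first screening step, before MRI and biological sampling.

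The cost is one reworded criterion, one screening question and a few more screen failures. In return, a foreseeable loss after allocation becomes an exclusion before entry, applied in the same way in all three arms.
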